## Abstract

**Trial registration:**

UMIN000028224; https://upload.umin.ac.jp/cgi-open-bin/ctr/ctr_view.cgi?recptno=R000032305.

## Introduction

Schizophrenia patients elicit a wide range of psychopathology, including psychotic symptoms, mood symptoms, and cognitive impairment (1–3). Several domains of cognitive function such as some types of memory, executive function, verbal fluency, and attention/information processing are impaired in schizophrenia (1, 2). Functional capacity is defined as the ability to perform everyday living skills, such as financial competence and communication in controlled and observational settings (3). By contrast, social function is influenced by several factors, such as opportunities and incentives in daily life (4). These levels of outcomes (cognitive function, functional capacity, and social function) have been reported to be related to each other (5, 6).

The UCSD Performance-based Skills Assessment-Brief (UPSA-B) is a scale of functional capacity linked to cognitive functioning in schizophrenia (5, 7). Patients with the illness demonstrate significantly lower scores on this scale compared with healthy controls, a finding pertinent to some of the non-Western countries, including Japan (5, 7).

Neuromodulation is defined as alterations of neural activity with targeted delivery of a stimulus, such as electrical stimulation or chemical agents, to specific neurological sites in the body. Neuromodulation techniques range from non-invasive approaches, e.g., transcranial magnetic stimulation, to invasive (implanted) devices, e.g., spinal cord stimulation and deep brain stimulation. For instance, transcranial direct current stimulation (tDCS) is a feasible and safe method, using weak and direct electrical current to the brain through electrodes (8, 9). Typically, two electrodes are placed over the scalp, through which anodal and cathodal stimulation increases and decreases cortical excitability, respectively. With this mechanism, tDCS has been suggested to modulate corticosubcortical/corticocortical pathways (10, 11).

tDCS has been shown to improve several domains of cognitive function in healthy subjects, stroke patients, and elderly individuals (12–17). Also, some studies reported facilitative effects of tDCS on learning memory, working memory, and verbal fluency in schizophrenia (18–20). Moreover, one sham-controlled randomized study has revealed that tDCS improved performance on the MATRICS Consensus Cognitive Battery in schizophrenia (21). On the other hand, little information is available about the effect of tDCS on functional capacity, as evaluated by a specific assessment tools, such as the UPSA-B.

In a previous open trial, we demonstrated the ability of tDCS to improve functional capacity, as well as depressive symptoms, in patients with schizophrenia (22). However, since this was a pilot study with a single arm, conducting a controlled trial is desirable. Therefore, we present a study protocol for a randomized controlled trial designed to evaluate the efficacy of tDCS on functional capacity in patients with schizophrenia.

## Material and Equipment

### Study Design

This is a single-center trial at Nacional Center of Neurology and Psychiatry, Tokyo, Japan (Figure 1). A two-arm, parallel-design, randomized controlled trial is planned, in which patients and raters will be blinded. Participants will be randomized with 1:1 ratio to either active or sham tDCS group with computer-generated sequence in the Electronic Data Capture (EDC) system. The superiority of active tDCS to sham tDCS will be investigated. Subjects will receive 10 sessions of active/sham tDCS in five consecutive days (twice per day). A participant’s allocation will be revealed by the principle investigator after the study endpoint. Results of the trial will be communicated by the study coordinators when requested.

**Figure 1 F1:**
[figure not shown]
Flowchart summarizing the trial procedure. ECT, electroconvulsive therapy; tDCS, transcranial direct current stimulation.

### Participants

Inpatients or outpatients treated at National Center Hospital, National Center of Neurology and Psychiatry will be enrolled. Subjects will be recruited by referrals from treating psychiatrists. They must provide written informed consent before starting the trial.

Subjects must meet the following inclusion criteria:
(1)DSM-5 criteria for schizophrenia(2)Being 18 through 70 years old

Patients with any of the following conditions will be excluded from the study:
(1)Alcohol or substance disorder(2)Past history of traumatic brain injury(3)Past history of epilepsy(4)Contraindicated to electroconvulsive therapy or tDCS(5)Scoring higher than 80 on the UPSA-B at baseline

The dose of neuroleptics will not be changed during the study period. In our pilot study (22), mean and SD of change from baseline of the UPSA-B was 11.68 (9.84) in patients scoring lower than 80 at baseline. We conservatively hypothesized that 9.00, the lower limit of 50% confidence interval of mean change from baseline in the pilot study, would be the mean difference between two groups in this study. In addition, Pearson correlation coefficient between the change and baseline value of the UPSA-B was estimated as −0.340. In these conditions, with a power of 0.9 for the primary analysis, an approximate number of 24 per group were estimated. Thus, considering study dropouts, a total sample of 50 was determined to be included.

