### Intervention

Direct current will be transferred by 35-cm^2^ saline-soaked sponge electrodes and delivered by Soterix Medical 1 × 1 Transcranial Direct Current Low-Intensity Stimulator Model 1300A. For each session, the tDCS montage will comprise placement of the anode over the left dorsolateral prefrontal cortex and the cathode over the contralateral supraorbital area, which corresponds to F3 and FP2 area, according to the International 10–20 electroencephalography system. We will apply 10 sessions of direct current of 2 mA for 20 min in five consecutive days (twice per day, 10:00 a.m. and 2:00 p.m.). The dose and frequency of stimulation were determined based on the pilot study (22).

For the sham group, the device will be turned off after 1 min of active stimulation. The electrode position and all the other procedures, including electrode moisture and checking the contact, will be identical to the conditions for the active-stimulation group. The display of the device will be kept outside participants’ vision field, and the device will be turned off blinded to subjects. A controlled study reports blinding integrity of tDCS and pharmacological treatment was comparable (23). The assessors and patients will be blinded to the treatment, and the contact between participants will be avoided to enhance the effect of study blinding.

Trained psychiatrists will administer tDCS. Since they will not be blinded, his or her interaction with participants will be minimized. Also, the experimenters will not participate in the assessment of outcome measures or any other aspects of the trial. To improve adherence, we will provide all consenting participants with costs of transportation and will remind and reschedule the visits of participants if necessary.

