## Stepwise Procedures

This protocol is presented in accordance with the 2013 SPIRIT (Standard Protocol Items: Recommendations for Interventional Trials) Statement, which was developed to provide guidance in the form of a checklist of recommended items to include in a clinical trial protocol to help improve the content and quality (25). This study was approved by Ethical Committee of National Center of Neurology and Psychiatry.

The schedule of enrollment, interventions, and assessments is summarized in Table 1. Participants will be recruited mainly by referrals from psychiatrists in National Center of Neurology and Psychiatry, Tokyo, Japan. We expect that two patients can be recruited per month on average, and that it will be possible to recruit 50 participants in 25 months.

All raters are well trained. All data will be administered in the EDC system, HOPE eACReSS, created by Fujitsu, Tokyo, Japan. Allocation and other identifiable data of subjects will be stored in a computer disconnected from Internet.

A review of previous studies indicates that most common adverse events included itching, tingling, headache, burning sensation, and discomfort (26). Experienced psychiatrists will check adverse effects before/immediately after every session, and evaluate the safety at every visit during the intervention. Data supervision using the EDC system will be conducted by an independent team of data managers and monitors.

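### The exclusion list bars patients contraindicated to tDCS but not those who have already received it, including the team's own open-label pilot participants, which is a small, cheaply closed gap in the blinding

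*Protocol article*

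**What the plan says.** The Participants section of the protocol article has two inclusion criteria (a DSM-5 diagnosis of schizophrenia and age 18 to 70) and five exclusion criteria. Two of the exclusions matter here: "Contraindicated to electroconvulsive therapy or tDCS" and "Scoring higher than 80 on the UPSA-B at baseline". Neither list mentions earlier tDCS or participation in the pilot. The one stated rule on other treatment is "The dose of neuroleptics will not be changed during the study period".

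The Introduction reports the team's own single-arm study: "In a previous open trial, we demonstrated the ability of tDCS to improve functional capacity, as well as depressive symptoms, in patients with schizophrenia". The Intervention section says that dose and frequency were taken from that pilot. Recruitment is local (Stepwise Procedures): "Participants will be recruited mainly by referrals from psychiatrists in National Center of Neurology and Psychiatry, Tokyo, Japan".

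Active sessions last 20 minutes at 2 mA. On the control arm the Intervention section says: "For the sham group, the device will be turned off after 1 min of active stimulation". To protect the blind, the device display is kept out of the patient's sight, contact between participants is avoided, the unblinded operators keep interaction to a minimum, and the raters are blinded. Patients are asked to guess their allocation once stimulation is complete (Outcome Measures).

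**The concern.** A contraindication is a reason why a patient should not receive a treatment. Previous treatment is a different matter, and a patient who had tDCS without trouble passes this criterion. A site applying the printed list would accept a pilot participant with a current UPSA-B score of 80 or below.

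The blind rests on patients being unable to tell 1 minute of current from 20. A patient new to tDCS has nothing to compare with. A pilot participant has: the pilot was open-label and single-arm, so everyone in it received known active stimulation, presumably of much the same length and strength because this trial's regimen was based on it. The stated safeguards act on what the patient sees and hears from others. They do not act on what the patient remembers feeling.

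The primary outcome is a performance test, so a patient who believes the treatment is sham may try less hard. That would lower sham scores and favour active tDCS. A second route is carry-over: a patient who keeps an earlier gain may have less left to gain, which shrinks the contrast between the arms.

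**Working it through.** **1. Reproduce the planned sample size.** Inputs from Participants: SD of change 9.84, correlation of change with baseline −0.340, difference 9.00, power 0.9, 24 per group. The analysis is ANCOVA on baseline (Anticipated Results). The article does not state alpha or sidedness, so two-sided 5% is assumed.

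- Residual SD = 9.84 × √(1 − 0.340²) = 9.25.
- Noncentrality at 24 per group = 9.00 / (9.25 × √(2/24)) = 3.37, with 2 × 24 − 3 = 45 degrees of freedom.
- Power = 0.909. At 23 per group it is 0.897. The stated 24 per group reproduces.

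**2. How many pilot patients could return?** The article does not give the pilot's size, but it can be inferred. Participants gives a mean change of 11.68 (SD 9.84) in those scoring below 80, and calls 9.00 the lower limit of a 50% confidence interval. Solve 11.68 − t(0.75, n−1) × 9.84/√n = 9.00:

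| n | lower limit (t) |
|---|---|
| 6 | 8.76 |
| 7 | 9.01 |
| 8 | 9.21 |

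So n is about 7. A normal quantile in place of t gives 8.97 at n = 6, so the answer is 6 or 7 either way. These patients gained 11.68 points on average. If the gain lasted, those who began close to 80 would now exceed it and be excluded.

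**3. Effect of dilution.** Assume a fraction f of patients is previously exposed and shows no new active-versus-sham difference, which is a pessimistic assumption. The expected difference becomes 9.00 × (1 − f). Power is given with the residual SD held at 9.25, and again with the variance raised for mixing patients with and without a response in the active arm: SD = √(9.25² + 0.5 × f(1 − f) × 9.00²).

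| Exposed | f | Difference | Power, SD 9.25 | Power, SD raised |
|---|---|---|---|---|
| 0 | 0 | 9.00 | 0.909 | 0.909 |
| 2 of 50 | 4% | 8.64 | 0.886 | 0.880 |
| 5 of 50 | 10% | 8.10 | 0.843 | 0.828 |

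The 10% row would need 5 of the roughly 7 pilot patients below 80 to return.

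**4. Effect of recognising the sham.** If a fraction f of sham patients recognises it and scores b points lower as a result, the bias towards active is f × b. The article gives neither figure, so both are assumptions. One of 25 sham patients (4%) gives 0.04 × 3 = 0.12 points for b = 3, and 0.04 × 9 = 0.36 points for b = 9. With 10% and b = 3 it is 0.30 points. All are small against the planned 9.00.

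**The case against.** The strongest reply is that this is an omission from a condensed article, that the full protocol may hold a further restriction, and that nothing shows a pilot patient will enrol. The pilot's site and dates are not stated. Admitting previously treated patients can also be a deliberate choice in favour of generalisability. Much of this stands and limits the size of the point. It does not remove it, because the article prints an explicit list of criteria and the point concerns what that list admits.

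The blinded raters and the end-of-treatment guess also count for the plan. The guess can reveal failed blinding, but it comes too late to prevent it.

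A reader might infer four stronger things that the documents do not support:

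- **That carry-over biases the comparison.** Earlier gain and earlier practice on the UPSA-B are baseline characteristics. Randomisation balances them in expectation, and the baseline covariate absorbs part of them. What remains is dilution, noise and chance imbalance, and dilution is conservative in a superiority test. Only recognition of the sham works differentially.
- **That a large share could be exposed, say 20%.** That is 10 of 50 patients, more than the whole inferred pilot subgroup of about 7. The bound does not cover tDCS received elsewhere, or pilot patients who scored 80 or more and have since fallen, but the article gives no sign of either.
- **That recent or concurrent ECT is an equal gap.** The criteria text is silent on it, but the legend of Figure 1 names ECT and the figure is not available here, so this cannot be confirmed.
- **That the harm could not be repaired afterwards.** The same team ran the pilot and participants are treated at the trial hospital, so pilot exposure should be traceable and a sensitivity analysis is possible. The absence of an item from a summary schedule does not show that exposure goes unrecorded.

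**Conclusion.** The point holds as a minor one. The printed criteria admit patients with earlier tDCS, including pilot participants scoring 80 or below, and the described blinding measures do not address what such a patient already knows. With 2 of 50 exposed and no new contrast in them, power falls from 0.91 to about 0.88 to 0.89. Bias from sham recognition would probably be a fraction of a point.

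This rests on a two-sided 5% test, on a pilot subgroup size inferred from the stated interval, and on an assumed share of exposed patients. No figure in the plan is wrong on this account, and no change in sample size follows.

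**What to change.** Add one exclusion criterion to Participants: any previous tDCS, including participation in the pilot study. Ask about it at the Week 1 eligibility screen and record the answer. If a previously exposed patient has already been randomised, keep that patient in the intention-to-treat set and add a sensitivity analysis of the UPSA-B comparison without such patients.

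This needs one eligibility line by amendment and one screening question. The downside is the loss of a few referrals, and perhaps slightly slower recruitment against the planned two patients per month.

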### Intervention

Direct current will be transferred by 35-cm^2^ saline-soaked sponge electrodes and delivered by Soterix Medical 1 × 1 Transcranial Direct Current Low-Intensity Stimulator Model 1300A. For each session, the tDCS montage will comprise placement of the anode over the left dorsolateral prefrontal cortex and the cathode over the contralateral supraorbital area, which corresponds to F3 and FP2 area, according to the International 10–20 electroencephalography system. We will apply 10 sessions of direct current of 2 mA for 20 min in five consecutive days (twice per day, 10:00 a.m. and 2:00 p.m.). The dose and frequency of stimulation were determined based on the pilot study (22).

For the sham group, the device will be turned off after 1 min of active stimulation. The electrode position and all the other procedures, including electrode moisture and checking the contact, will be identical to the conditions for the active-stimulation group. The display of the device will be kept outside participants’ vision field, and the device will be turned off blinded to subjects. A controlled study reports blinding integrity of tDCS and pharmacological treatment was comparable (23). The assessors and patients will be blinded to the treatment, and the contact between participants will be avoided to enhance the effect of study blinding.

Trained psychiatrists will administer tDCS. Since they will not be blinded, his or her interaction with participants will be minimized. Also, the experimenters will not participate in the assessment of outcome measures or any other aspects of the trial. To improve adherence, we will provide all consenting participants with costs of transportation and will remind and reschedule the visits of participants if necessary.

### Outcome Measures

Patients will be assessed after being informed of the objectives of the study and providing their informed consent to participate. Data will be collected following an assessment that will be implemented at baseline, immediately after the last stimulation, and 1 and 2 months thereafter (see Table 1). Baseline and follow-up evaluations will be performed by experienced psychologists blinded to group allocation.

**Table 1 T1:** Study schedule.

	Study period							
	Enrollment	Intervention					Follow-up 1	Follow-up 2

Time point	Week 1	Week 2					Week 6	Week 10
		Day 1	Day 2	Day 3	Day 4	Day 5		
**Enrollment**								
Eligibility screen	X							
Informed consent	X							
Sociodemographic characteristics	X							
**Intervention**								
Transcranial direct current stimulation (twice/day)								
**Assessments**								
UPSA-B	X					X	X	X
BACS	X					X	X	X
PANSS	X					X	X	X
Adverse events	X						X	X

*UPSA-B, the UCSD Performance-based Skills Assessment-Brief; BACS, the Brief Assessment of Cognition in Schizophrenia; PANSS, Positive and Negative Syndrome Scale*.

#### Functional Capacity (Daily-Living Skills)

The primary outcome is functional capacity evaluated by the UPSA-B (7), which consists of Finance and Communication subscales.

#### Cognition

Cognitive function will be assessed by the Brief Assessment of Cognition in Schizophrenia (BACS), which includes tests of verbal memory (Verbal Memory Task), verbal working memory (Digit Sequencing Task), motor/speed (Token Motor Task), verbal fluency (Verbal Fluency Task), attention/information processing (Symbol Coding Task), and executive function (Tower of London Task). To provide a standard metric for combining test scores into domains and comparing performance over time, BACS scores will be converted to *z*-scores, which shows relative outcomes compared with those of healthy people (1). Alternative forms will be used for Verbal Memory Task and Tower of London Task at baseline and follow-up assessments.

#### Psychotic Symptoms

Psychotic symptoms will be evaluated by the Positive and Negative Syndrome Scale (PANSS), commonly used for the assessment of psychotic symptoms of schizophrenia (24). It consists of Positive Syndrome, Negative Syndrome, and General Psychopathology subscales.

To ensure the success of blinding, we will ask patients to guess whether the treatment was active or sham after the stimulation procedure has been completed.

## Stepwise Procedures

This protocol is presented in accordance with the 2013 SPIRIT (Standard Protocol Items: Recommendations for Interventional Trials) Statement, which was developed to provide guidance in the form of a checklist of recommended items to include in a clinical trial protocol to help improve the content and quality (25). This study was approved by Ethical Committee of National Center of Neurology and Psychiatry.

The schedule of enrollment, interventions, and assessments is summarized in Table 1. Participants will be recruited mainly by referrals from psychiatrists in National Center of Neurology and Psychiatry, Tokyo, Japan. We expect that two patients can be recruited per month on average, and that it will be possible to recruit 50 participants in 25 months.

All raters are well trained. All data will be administered in the EDC system, HOPE eACReSS, created by Fujitsu, Tokyo, Japan. Allocation and other identifiable data of subjects will be stored in a computer disconnected from Internet.

A review of previous studies indicates that most common adverse events included itching, tingling, headache, burning sensation, and discomfort (26). Experienced psychiatrists will check adverse effects before/immediately after every session, and evaluate the safety at every visit during the intervention. Data supervision using the EDC system will be conducted by an independent team of data managers and monitors.

## Anticipated Results

As discussed earlier, we anticipate that 9.00 will be the mean difference in the UPSA-B between two groups. Statistical analysis will be conducted using SAS 9.4, created by SAS Institute Inc., NC, USA. We will handle missing data with last observation carried forward method as an intention-to-treat analysis for all participants allocated. We will also perform a per protocol approach as a sensitivity analysis for the comparison of the results. For the UPSA-B, BACS, and PANSS, we will use analysis of covariance regarding each value at baseline as a covariate.

Functional capacity, or daily-living skills, has been reported to provide one of the most important factors affecting social consequences in patients with schizophrenia (6, 27). As stated before, tDCS is a safe method of brain stimulation and has been reported to improve several domains of cognition in schizophrenia (18–22). In addition, our pilot open study (22) demonstrated tDCS improved functional capacity, as measured by the UPSA-B. So far, no controlled trial has been performed to investigate the effect of tDCS on this level of functional outcome. Therefore, the randomized controlled trial described in this article is expected to provide a strategy to enhance social consequences in patients with schizophrenia.

The topic of adherence might be regarded as a potential pitfall in this protocol. However, as mentioned before, by adding costs of transportation for all included patients to the study budget, we plan to compensate for this issue. Also, the study coordinator will remind and reschedule all visits of participants as needed.

We believe that this is a well-designed controlled trial to test the ability of tDCS to improve an important determinant of outcome in patients with psychiatric disorders. Even if the results do not prove our hypothesis, the gathered data will contribute to a field that has not been widely studied.

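### Last observation carried forward as the intention-to-treat analysis can bias the group difference in either direction, and no planned analysis tests its assumption

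*Protocol article*

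**What the plan says.** Under Anticipated Results the protocol article fixes the handling of missing data: "We will handle missing data with last observation carried forward method as an intention-to-treat analysis for all participants allocated". For UPSA-B, BACS and PANSS, "we will use analysis of covariance regarding each value at baseline as a covariate". The one sensitivity analysis named is this: "We will also perform a per protocol approach as a sensitivity analysis for the comparison of the results".

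Under Functional Capacity, "The primary outcome is functional capacity evaluated by the UPSA-B". Under Outcome Measures, assessments are "implemented at baseline, immediately after the last stimulation, and 1 and 2 months thereafter". The first post-baseline score is therefore taken on Day 5, at the end of a five-day course, and the two later scores are taken when no stimulation is being given. The article does not say which visit is primary, so both possibilities are worked through below.

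**The concern.** The missing-data rule is stated, so it is not a detail left to an unseen analysis plan, and no reason is given for it.

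The rule does different things at different visits. A patient lost before the Day 5 assessment is given the baseline score, so the change is set to zero. A patient lost after Day 5 is given a score taken at or nearer the end of stimulation, which then stands in for the 1- or 2-month score. Whether benefit outlasts a five-day course is what the follow-up visits are there to show, and the rule assumes for these patients that it does.

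The direction of any bias therefore depends on the visit, so the rule cannot be defended as conservative throughout. The per-protocol analysis does not settle the matter. It changes which patients are analysed, after randomisation, and does not vary what is assumed about the missing scores. Agreement between the two analyses would not validate the carried values.

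**Working it through.** **Inputs from the article.** Participants: "mean and SD of change from baseline of the UPSA-B was 11.68 (9.84) in patients scoring lower than 80 at baseline" and "Pearson correlation coefficient between the change and baseline value of the UPSA-B was estimated as −0.340"; power 0.9; 24 per group, 50 in total. Anticipated Results: "we anticipate that 9.00 will be the mean difference in the UPSA-B between two groups".

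**Assumptions not in the article.** Two-sided 5% level; 25 per arm; baseline SD 12; correlation 0.7 between visits after baseline adjustment; dropout of 4% to 30%, unrelated to outcome within arm; the fading pattern used in step 4. The power figures also assume a sham gain of 3 points.

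**1. The plan's own figure.** SD given baseline = 9.84 × √(1 − 0.340²) = 9.25. Normal formula: n = 2 × 9.25² × (1.960 + 1.282)² / 9.00² = 22.2, so 23 per group. With the noncentral t, power is 0.897 at 23, 0.909 at 24 and 0.920 at 25. The stated 24 is reproduced. The dropout allowance is (50 − 48)/50 = 4%.

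**2. Bias formula.** In each arm, the shift equals the share of leavers times (mean at the carried visit − mean at the target visit). The bias is the active shift minus the sham shift. With an equal dropout share p in both arms it becomes p × (group difference at the carried visit − group difference at the target visit), and any gain common to both arms cancels.

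**3. Target Day 5, true difference 9.** Baseline is carried, so the expected estimate is 9(1 − p).

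**4. Target 2 months, difference 9 at Day 5, 4.5 at 1 month, 0 at 2 months.** If half the leavers go after Day 5 and half after 1 month, the bias is (p/2) × 9 + (p/2) × 4.5 = 6.75p. If all go straight after Day 5, it is 9p.

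| Dropout per arm | Day 5 estimate (true 9) | 2 months, even split (true 0) | 2 months, all after Day 5 (true 0) |
|---|---|---|---|
| 4% | 8.64 | 0.27 | 0.36 |
| 10% | 8.10 | 0.68 | 0.90 |
| 20% | 7.20 | 1.35 | 1.80 |

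Simulation agrees. Day 5 gives 8.64, 8.0 to 8.1, and 7.2. At 2 months with all leaving after Day 5 it gives 0.36, 0.89 and 1.81, with rejection of 5.2%, 6.5% and 9.9%. The even split at 20% gives about 1.4, with rejection of about 8%. ANCOVA on observed scores gives about 9 and about 0 respectively, with rejection near 5% in the second case.

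**5. Unequal dropout.** Take 30% active and 10% sham, the same fading, a flat sham arm and an even split. The bias is 0.15 × 9 + 0.15 × 4.5 = 2.03, with rejection of about 11%.

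**6. Cases without bias.** With a 9-point effect that lasts and a post-stimulation value carried, the estimate stays at about 9.0 at both 4% and 20% dropout. With no effect at any visit and equal dropout, it stays near 0 with about 5% rejection.

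**7. Standard error at 20% dropout.** Counting all 50 patients as observed: 9.25 × √(2/25) = 2.62. Counting the 40 actually observed: 9.25 × √(2/20) = 2.93. Simulated values are about 2.6 to 2.7 for carried-forward data (2.49 at the lowest, for Day 5 in a second set of runs) against about 2.96 for observed data. The carried-forward standard error nevertheless matches that estimator's own sampling SD: 2.63 against 2.63 with no effect, 2.58 against 2.61 in another run.

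**8. Power at Day 5.** Complete data give 0.92. At 10% and 20% early dropout, observed-data ANCOVA gives about 0.87 and 0.84, and carried-forward data about 0.84 and 0.78. The loss due to the method is 0.87 − 0.84 = 0.03 and 0.84 − 0.78 = 0.06. The remaining 0.05 and 0.08 come from dropout itself.

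Observed-data ANCOVA served as a stand-in for a likelihood-based analysis in these comparisons.

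**The case against.** Four points can fairly be made for the plan.

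- **The bias is conditional.** A reader might infer that carrying forward always biases the result. It does not: step 6 shows none when the effect lasts or is absent and dropout is random and equal. Practice gains common to both arms also cancel under equal dropout. This stands.
- **The standard error.** A reader might infer that the reported standard error is wrong and the test generally too liberal. Step 7 does not support that. The standard error is right for the carried-forward estimator and is only smaller than the observed data would support. The excess rejection in steps 4 and 5 comes from bias. This stands.
- **Dropout may be low.** The article allows only about 4% and plans transport costs, reminders and rescheduling. The larger figures need dropout of 10% to 30%, and the 2-month figures also need complete fading; none of this is in the article. This stands as to size. However, the article itself calls adherence a possible pitfall, and it gives no rate that would rule out 10% or 20%.
- **Day 5 may be primary.** The main result would then be pulled toward zero under similar dropout, which works against a false superiority claim, and the false persistence would touch only later visits. Much of the power loss would also occur under any method, since a patient with no post-baseline score cannot be recovered. This stands, but an attenuated primary estimate is still biased, and unequal dropout can change its direction.

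None of this supplies a reason for the rule or an analysis that tests it.

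**Conclusion.** The point holds as a conditional one. The stated rule can bias the difference toward zero at Day 5 and toward a false lasting effect at 1 or 2 months, and the per-protocol comparison cannot show which has happened.

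The size depends on a dropout rate that the article does not give. At the implied 4% the effect is negligible. It becomes material at assumed rates of 10% to 20%: up to 1.8 of the 9 points at Day 5 or, at 20% with complete fading by 2 months, about 1.4 points where the truth is zero. At Day 5 the method itself costs about 0.03 to 0.06 of power.

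The documents do not support saying that the trial's result will be biased, that its standard error is invalid, or that the whole power loss is due to the method. The planned sample size is unaffected. This is a change that should be made, because the remedy is cheap and the rule has no stated justification.

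**What to change.** Replace carrying forward as the main analysis by one of two options:

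- a likelihood-based repeated-measures model on the three post-baseline scores, adjusted for baseline, with the group contrast read at the primary visit; or
- multiple imputation by arm, followed by the planned ANCOVA at that visit.

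Either way, keep all allocated patients. A repeated-measures model with baseline only as a covariate drops those without any post-baseline score, so they need imputation or a model that treats baseline as one of the outcomes. Apply the same handling to BACS and PANSS, which fall under the same rule.

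Add one sensitivity analysis that varies the missing-data assumption, such as delta-adjusted or sham-reference imputation. Label the per-protocol analysis as supplementary. Carrying forward may stay as a secondary check.

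The cost is revised wording and slightly more programming in SAS 9.4, which the article already names. No visits, patients or data are added. The standard error will be slightly larger, because missing scores no longer count as observed. The change should be made before unblinding.
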